## Abstract

The incidence of stroke has increased significantly in recent years. Post-stroke hemiplegia is a common stroke complication with long-term negative consequences. Several studies have suggested that acupuncture could be an effective intervention for the rehabilitation of post-stroke hemiplegia. Intradermal needling is a kind of acupuncture which is widely used in clinical settings. This study attempts to investigate the biomechanical effects of intradermal needle for post-stroke hemiplegia recovery.

This proposed study is a single-centered, prospective, single-blinded (patient-assessor-blinded), randomized clinical pilot trial involving 40 patients with post-stroke hemiplegia. Patients will be randomized to an experimental group or control group in a 1:1 ratio. All of them will receive conventional rehabilitation therapies. Patients in the experimental group will be treated with intradermal needle, whereas patients in the control group will receive sham intradermal needle. The primary outcome measures will be biomechanically validated from the parameters of RSSCAN gait system: plantar pressure distribution, step length, and stride. The scores of clinical scales such as National Institutes of Health Stroke Scale, Fugl-Meyer Assessment, Berg Balance Scale, Barthel Index, and Stroke-specific Quality of Life Scale will be assessed as secondary outcome measures. All assessments will be conducted at baseline, 4 weeks after intervention and at the end of 3 months’ follow-up.

The purpose of this study is to explore the potential effect and biomechanical mechanisms of intradermal needle for post-stroke hemiplegia recovery, as well as to provide a basis for future larger clinical studies.

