### Sample size

2.3

Out study is a preliminary clinical trial aiming to evaluate the feasibility of intradermal needle therapy for post-stroke hemiplegia recovery. Therefore, we did not determine sample size basing on statistical calculations.^[22]^ An alternative approach to estimate the sample sizes for pilot studies with 10 to 40 patients per group was adopted.^[23]^ Accordingly, to exceed the minimal number and combine with the actual situation, a total of 40 patients will be recruited in this research, 20 in each group. Assuming a 20% drop-out rate, we aimed to recruit 50 patients. Each group will require 25 initial participants.

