### Statistical analysis

2.18

Statisticians will be responsible for the statistical analysis. The main analysis will compare the changes in all outcome measurements of between-group or within-group to evaluate the effect of intradermal needle treatment. An intention-to treat analysis will be conducted using the SPSS (Statistical Product and Service Solutions) program (version 22.0, Chicago, IL). Continuous variables will be expressed as means ± standard deviations, Wilcoxon rank sum tests with no adjustment for multiple comparisons will be used for comparisons. Categorical variables will be presented with frequencies or percentages. Fisher exact test will be applied in testing blinding between groups because of small cell counts. A *P* value of <.05 (2-sided) is considered to indicate statistical significance, with 95% confidence intervals.

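### Outcomes are compared as changes by an unadjusted rank-sum test; adjusting for baseline would usually be more precise and would yield the mean difference that the promised 95% confidence intervals need

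*Protocol article*

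**What the plan says.** The protocol's Statistical analysis section (2.18) fixes the contrast: the main analysis will "compare the changes in all outcome measurements", between groups or within groups. It fixes the test: "Wilcoxon rank sum tests with no adjustment for multiple comparisons will be used for comparisons". It fixes the summary: "Continuous variables will be expressed as means ± standard deviations". It closes with a two-sided threshold and intervals: "value of <.05 (2-sided) is considered to indicate statistical significance, with 95% confidence intervals". No covariate or model is named, and the intervals are not tied to any estimate.

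The Outcome measures section (2.11) has every outcome examined at baseline, after the 4-week treatment and at the end of the 3-month follow-up, so a baseline value is available for each. The Sample size section (2.3) plans for 40 patients, 20 per group, with 50 recruited, and says that the number does not come from a statistical calculation. The randomisation section (2.8) describes a computer-generated 1:1 list and names no stratification. The Abstract gives as one purpose of the trial "to provide a basis for future larger clinical studies".

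**The concern.** The method is stated, so it can be judged as it stands, whatever a separate analysis plan adds. There are two weaknesses.

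The first is precision. A change score in effect assumes a slope of 1 of follow-up on baseline. With equal variances the true slope is rho, which is below 1, so the change score over-corrects. Part of any chance baseline difference between arms then carries over, with reversed sign, into the estimated effect. With about 20 per arm and no stratification described, such differences will not be negligible.

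The second is that test and estimate do not match. A rank-sum test compares ranks; it does not estimate a difference in means. The summaries are means with SDs, and 95% intervals are promised without saying what they are intervals for. A pilot of this kind chiefly passes on an effect estimate, its uncertainty and an SD for planning. Those should come from the same analysis as the test.

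**Working it through.** **Inputs from the protocol.** 20 evaluable patients per arm, 20% drop-out, 50 recruited (Sample size); rank-sum test on change, two-sided 0.05 (Statistical analysis).

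**Assumptions, not in the protocol.** Correlation rho between baseline and follow-up from 0.3 to 0.9; equal SD at both times, set to 1; illustrative effects of 0.5 and 0.7 SD. The protocol gives no correlation, SD, effect size or power, so no power figure of its own can be reproduced.

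**Step 1: the plan's own figure.** 40/(1 − 0.20) = 50, and 20/(1 − 0.20) = 25 per group. Both match the protocol.

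**Step 2: variance.** Per-patient variance is 2(1 − rho) for the change score and 1 − rho² for ANCOVA. The ratio is (1 − rho²)/[2(1 − rho)] = (1 + rho)/2. The per-arm number at which ANCOVA matches 20 per arm on change is 20 × (1 + rho)/2.

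**Step 3: expected 95% CI half-width at 20 per arm, in SD units.** Change: t(0.975; 38) × √[2(1 − rho) × 2/20]. ANCOVA: t(0.975; 37) × √[(1 − rho²) × 2/20] × √(1 + 1/36), where the last factor is the cost of estimating the slope.

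| rho | variance, change | variance, ANCOVA | ratio | matching n per arm | half-width, change | half-width, ANCOVA |
|---|---|---|---|---|---|---|
| 0.3 | 1.40 | 0.91 | 0.65 | 13 | 0.757 | 0.620 |
| 0.5 | 1.00 | 0.75 | 0.75 | 15 | 0.640 | 0.563 |
| 0.7 | 0.60 | 0.51 | 0.85 | 17 | 0.496 | 0.464 |
| 0.9 | 0.20 | 0.19 | 0.95 | 19 | 0.286 | 0.283 |

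**Step 4: chance imbalance.** The standard error of the baseline difference between arms is √(2/20) = 0.32 SD. The change score carries over (1 − rho) times the imbalance. At rho 0.5, a one-standard-error imbalance shifts the estimate by 0.5 × 0.32 = 0.16 SD. This is extra noise, not bias: it averages to zero over randomisations.

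**Step 5: simulated power with normal data, 20 per arm, rank-sum on change versus ANCOVA.**

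- Effect 0.5 SD: 23% v 35% (rho 0.3), 32% v 41% (0.5), 50% v 57% (0.7), 92% v 94% (0.9).
- Effect 0.7 SD: 41% v 61% (rho 0.3), 55% v 69% (0.5), 76% v 84% (0.7), 92% v 95% (0.8).

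**Step 6: the same comparison with non-normal residuals, effect 0.7 SD.** The ordering can reverse.

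- t residuals with 3 degrees of freedom: 91% v 86% at rho 0.7 and 99% v 94% at 0.8, in favour of the rank-sum test.
- Lognormal residuals: 81% v 77% at rho 0.5 and 98% v 87% at 0.7, again in favour of the rank-sum test.
- At rho 0.3 ordinary ANCOVA still had more power in both cases.
- A rank-based ANCOVA clearly beat the rank-sum test on change at rho 0.3 to 0.5, and stayed within about 3 percentage points of it at 0.7 to 0.8.

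**The case against.** The strongest defence is that a distribution-free test is a sensible choice in a small pilot with plantar pressures and bounded scales, and that ordinary ANCOVA leans on normality. Step 6 shows that this has force: with heavy tails or marked skew and a moderate to high correlation, the rank-sum test on change has more power than ordinary ANCOVA. The protocol does not describe the distribution of its gait measures. What stands is that the power gain is conditional. What does not follow is that baseline should be left unadjusted, because ranks can be adjusted for baseline too. It is also fair to say that power matters less in a trial not sized by power, but a narrower interval matters in any pilot that feeds planning.

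Three stronger readings are tempting, and the protocol does not support them.

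- A reader might infer that baseline is ignored. It is not: a change score subtracts it. The point is that the analysis does not condition on it.
- A reader might infer that no interval will be given. The section promises means with SDs and 95% intervals, and a mean difference could be derived from them. The gap is that no estimate is named and the test does not supply one.
- A reader might infer that every patient with a missing visit is dropped, contrary to "An intention-to treat analysis will be conducted". No complete-case rule is stated, and imputation is neither stated nor excluded. A patient with week-4 data but no follow-up would still give a week-4 change. Handling of missing data is commonly left to an analysis plan, which is not shown here. Even if the expected 20% were left out, 50 × 0.80 = 40, the number planned for.

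**Conclusion.** The point holds as a recommendation on efficiency and reporting. Under equal variances, not conditioning on baseline costs 35%, 25%, 15% or 5% of the effective sample at rho 0.3, 0.5, 0.7 or 0.9 (one minus the variance ratio). The loss is worth recovering at low to moderate correlation and close to nil at 0.9. These sizes rest on assumed correlations. The power advantage of ordinary ANCOVA over the rank-sum test further assumes roughly normal data; without that, the case for baseline adjustment rests on the rank-based form. The mismatch between a rank test and intervals tied to no estimate does not depend on any of these assumptions. The planned comparison is a valid test and remains unbiased over randomisation.

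**What to change.** For each gait parameter and clinical scale, analyse the week-4 value and the end-of-follow-up value by ANCOVA with arm and the baseline value of that outcome. Report the baseline-adjusted mean difference with its 95% CI, and the residual SD for planning the larger trial. Where data are skewed or heavy-tailed, use a rank-based ANCOVA (ranks of the outcome adjusted for ranks of baseline) as the test or as a sensitivity analysis, and state in advance which role it has. A mixed model over both visits is optional and not needed for this point.

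The cost is a change of analysis wording, slightly more analysis work, and a normality assumption for the mean-based estimate. No further patients, visits or measurements are needed, and the named software can run it. The Trial status section reports enrolment as still under way, so as of the article the change could be fixed before unblinding.

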### Dissemination

2.19

The result of this study will be published regardless of the direction of the effect.

## Discussion

3

Hemiplegia is the most common symptom of stroke. The typical feature of this disease is that the apraxia will exist and continue for several weeks, months, or years. It causes a heavy burden on both healthcare resources and the society. Cohort studies have consistently reinforced the importance of post-stroke rehabilitation to stimulate recovery.^[34]^ Acupuncture is considered as a frequently used therapy to harmonize and regulate the functional activities of the brain and body. Previous studies have indicated that acupuncture combined with conventional rehabilitation therapies is more effective for post-stroke patients.^[35]^ However, the treatment of acupuncture is carried out at clinic, lasting temporarily. Patients cannot receive any therapeutic measures besides this period. Thus, therapies that can maintain for longer time are required.

Intradermal needle, with the advantages of convenience, little pain, long-lasting, satisfactory effects, and few adverse reactions, is attracting increasing clinical attention.^[36]^ It is inserted and affixed in superficial skin, which is densely packed with sensory and motor neurons. The nerves of skin are associated with brain. It can be transmitted to central nervous system when someone stimulates the acupoints on the skin. The cerebral center integrates the information and corresponds through homologous movement.^[37]^ In the aspect of different needle-retaining, some researchers randomly divided 251 ischemic apoplexy patients into 20, 40, and 60-minute groups. Through the results of hemorheological values, the therapeutic effect of 60-minute group was the best.^[38]^ Intradermal needle is a kind of superficial needling, which can be maintained for 1–3 days, so as to extend the effect of acupuncture. It is therefore of great clinical significance that our study uses intradermal needle therapy to treat post-stroke hemiplegia.

In clinical studies, evaluations play an important role. A majority of previous studies adopt clinical rating scales to estimate the therapeutic effect, which have been proven to be prone to some errors associated to the evaluators’ subjective perception.^[39]^ Lack of objective assessments affects the quality of results.^[40]^ To overcome this limitation, this study may potentially confirm whether or not intradermal needle is effective for post-stroke hemiplegia by using biomechanical outcome measurements from the RSSCAN gait system. It can provide objective kinematic data of static and dynamic gait. Vertical plantar pressure dispersion of the foot will be recorded, processed, and graphically displayed in terms of sequential gait changes.^[41]^ It helps to remove some of the unavoidable guess work from essential diagnostic and therapeutic procedures. Our previous work has shown that it is affordable, accurate, and reliable for the assessment of motor function in patients with stroke.^[42]^

The unavoidable limitations of our trial consist of three domains. First, despite the assessor-blinding, some patients who got treated with intradermal needles will likely know which group they are in. Therefore, we will select participants who have never used these needles and keep participants separate from each other during the treatment procedure. Next, after completion of the 4-week treatment, a 3-month follow-up will be conducted. This time span means that participants’ compliance could be a problem. Thus, we designed a recover diary and regular telephone follow-up to minimize this situation. The last limitation is the small sample size, as this trial was proposed to be a pilot study for further larger scaled clinical study.

This study focuses on the biomechanical effect of intradermal needle embedding for post-stroke hemiplegia, so far there is no study of this aspect. If the trial is successfully carried out, we may provide feasibility data and basic information for utilizing this therapy and build a stronger foundation for other studies.

### Trial status

3.1

This trial started on 1 May 2016 and is currently in the participants’ enrollment.
